### Arms and interventions

Upon enrolment into the study, both the intervention and control groups receive leaflets with information about PSD, along with the advice to seek help, via emergency phone numbers or websites, if they have such symptoms. Patients in the interventional group receive the active intervention, patients without confirmation of a depressive episode are assigned to the intention to treat group. Intervention and control groups receive weekly phone calls over a period of 12 weeks, at the earliest time point of eight weeks after the acute stroke.

The intervention group receives a Behavioural Activation (BA) therapy. The intervention follows the BA procedure used in the Change PDD study (a psychotherapy study funded by DFG (Deutsche Förderungsgemeinschaft)). In each phone call, techniques will be taught, structured, and attempted to be integrated into the patients’ daily lives in an accessible and gradual manner. The phone calls last 25 min and are conducted by BA-trained professionals with access to regular supervision by BA-certified psychologists.

The control group is contacted at the same time as the intervention group after the index event. At 84, 180 and 365 days after inclusion standardized postal questionnaires are sent to the patients. The phone contacts match the frequency and scope of the intervention group. The control group will receive guided mindfulness-based practices conducted by trained professionals.

Irrespective of the allocation, all patients will receive a state-of-the-art treatment according to the guidelines of secondary stroke prevention. They receive counselling and education on stroke pathophysiology, risk factor management, lifestyle improvement and medication compliance by a stroke specialist. Only selected high-risk patients are seen in the outpatient clinic of the stroke center. The patient’s general practitioner manages post discharge risk-factor management. This also covers the recommended therapies for comorbidities after stroke, such as post stroke depression, fatigue etc. Additional treatments are not part of the study.

The above-mentioned interventions are unlikely to cause any somatic side effects. Mental decompensations are conceivable. To address this, we provide the patients with an emergency contact (phone number), which will be available 24/7. We hypothesize, that the intervention might be effective but randomization into the control arm will not cause any lower quality of care as patients in the control arm will get standard stroke care plus standardized information material.

### Outcome measures

#### Primary outcomes

Change in Patient Health Questionnaire-9 (PHQ-9) score from Baseline (V1) to day 84 (V2).

#### Secondary outcomes

Change in Patient Health Questionnaire-9 (PHQ-9) score from Baseline (V1) to days 84, 180 (V2, V3) and 365 (V4).Change in EuroQol- 5 Dimension (EQ-5D) score from Screening (V0) to days 84, 180 and 365 days (V2-V4).Change in modified Rankin Scale (mRS) from Screening (V0) to days 84, 180 and 365 (V2-V5).Return to work from Screening (V0) to days 84, 180 and 365 days (V2-V4).Incidence of major cardiovascular events defined as nonfatal stroke (ischemic or hemorrhagic), nonfatal myocardial infarction (including acute coronary syndrome requiring emergency vascularisation), and vascular death (i.e. sudden cardiac death and death from acute myocardial infarction, ischemic or hemorrhagic stroke, heart failure, cardiovascular procedures, pulmonary embolism, or peripheral artery disease) within one year of the index event.Recurrent ischemic or hemorrhagic stroke or TIA (transient ischemic attack; defined as transient neurological deficit < 24 h and absence of DWI (Diffusion-weighted imaging) positive lesions on MRI (Magnetic resonance imaging)) within one year of the index-event.All-cause mortality at 14 months.

Regular mortality follow-ups will be done for gathering information on deaths in the study sample. Death-certificates will be provided by local health authorities, causes of death will be specified using the International Classification of Diseases (ICD)-11.

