### Study description and study design

We compare the efficacy of telepsychological Behavioural Activation (BA) therapy with guided mindfulness-based practices for patients with PSD in this monocentric, randomized, controlled, rater-blinded trial. The allocation ratio is 1:1. Repeated follow-ups are planned up to one year after enrolment to assess short- and long-term effects.

Baseline characteristics such as age, sex, cerebrovascular risk factors, history of relevant diseases, history of preceding strokes, stroke etiology, stroke severity (NIHSS and modified Rankin scale (mRS)) at admission and discharge and acute stroke treatment will be gathered from the patients’ chart.

Following the screening visit (V0), patients with persisting depressive symptoms after eight weeks (56 days) at the baseline visit (V1) are randomized either to the intervention or the control condition and are invited to three more visits until the end of study visit (V4, day 365). The primary outcome is evaluated at visit 2 (day 84), the secondary outcomes at the end-of study visit (V4). Table 1 shows the detailed scope and the frequency of study visits.

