The intention-to-treat (ITT) population includes all patients as randomized, and the modified intention-to-treat (mITT) population includes all patients as randomized + having received the first visit after signed informed consent (baseline visite). The safety population includes all patients as randomized. Assuming a drop-out rate of 10% during the intervention period, 76 patients are planned to be randomized. The per protocol (PP) population will include all participants without major protocol violations. All primary analyses will be performed on the ITT population. For the primary endpoint, a linear mixed model will be performed and in cases of significant ‘group x time’ interactions, post-hoc comparisons corrected for multiple testing will be performed. Continuous secondary endpoints will be analysed using linear mixed models and subsequent post-hoc tests if the requirements for this strategy are met (tested by Kolmogorov-Smirnov tests and Levene’s tests). In cases where the assumptions of normality or variance homogeneity are violated, a monotonic transformation of variables will be performed. If this first step is not successful, corresponding non-parametric tests will be used. Side-effects, adverse events (AE) and severe adverse events (SAE) will be analysed with descriptive statistics and likelihood-ratio tests. Demographic information will be shown for each group separately, and they will be compared between the groups. Dichotomous variables will be analysed with likelihood-ratio tests and continuous variables will be analysed using analyses of variance or respective non-parametric tests. Baseline characteristics are presented as mean (M) ± standard deviation (SD) for normal distributed and additionally median and 25th and 75th quartiles (Q25, Q75) for all continuous variables. Categorical variables are given as numbers (n) and percentages (%). An interim analysis is not planned. The statistician will be blinded for the groups during the phase of data-analyses. Prior to the start of the trial, a statistical analysis plan will be developed.

All analyses will be performed at a significance level of α = 0.05.

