### Eligibility criteria

All patients with acute ischemic or hemorrhagic stroke admitted to the Neurology Department at the University Hospital of Augsburg will be screened for depressive symptoms during the first days of their hospital stay as part of the DESIE (Depression bei somatischen Erkrankungen) Study. Here, a PHQ-9 cut-off score of ≥ 10 was found to have a high sensitivity (91%) and specificity (89%) for major depression and any other depression diagnosis (78% / 96%) [18]. Patients are eligible for inclusion irrespective of whether the index event was a first or recurrent event. Ischemic stroke is ascertained using criteria based on clinical and/or imaging features. Patients with transient ischemic attacks are excluded from the study, as they do not have persisting stroke symptoms. These patients might probably not benefit from the intervention and might distort effects between the intervention or control group. For study inclusion, patients must give their written informed consent. Patients, who cannot give informed consent, e.g. because of dementia or aphasia, are not eligible. Neither are patients with legal guardians, those with premorbid mRS of > 2, or patients with a shorter life-expectancy than the expected duration of the trial, e.g. due to malignancy or other severe diseases.

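### The mRS endpoint is worded as a change from an acute value taken about eight weeks before randomisation; adjusting for that value instead would recover precision at almost no cost

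*Protocol article*

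**What the plan says.** Under Secondary outcomes, the Protocol article lists "Change in modified Rankin Scale (mRS) from Screening (V0") to days 84, 180 and 365, with the visits labelled V2 to V5. The last label looks like a slip, since Study description and study design makes V4, day 365, the final visit.

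Timing of the reference value: under Eligibility criteria, patients "will be screened for depressive symptoms during the first days of their hospital stay". Under Study description and study design, "patients with persisting depressive symptoms after eight weeks (56 days) at the baseline visit (V1) are randomized". The same section says that "stroke severity (NIHSS and modified Rankin scale (mRS)) at admission and discharge" comes from the chart. The readable text does not say which of these grades serves as the V0 value.

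Analysis: in the statistical paragraphs after Table 1, "Continuous secondary endpoints will be analysed using linear mixed models and subsequent post-hoc tests if the requirements for this strategy are met", as judged by Kolmogorov-Smirnov and Levene tests. Otherwise a monotonic transformation is tried, and if that fails, "corresponding non-parametric tests will be used". Dichotomous variables go to likelihood-ratio tests. No route is named for ordinal outcomes, mRS is not assigned to any route, and covariate adjustment for a starting value is not mentioned. A separate statistical analysis plan is announced but is not available here.

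**The concern.** The mRS is an ordinal grade, so a difference of one step does not mean the same along the scale. A patient at grade 1 can improve by one step only, and a patient at grade 4 by four.

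The larger issue is the reference point. Change from V0 includes roughly eight weeks of recovery that took place before anyone was randomised. Randomisation keeps the comparison unbiased, but that early recovery enters the outcome as noise. If the V0 and later grades correlate only moderately, subtracting V0 can add more variance than it removes, whereas adjusting for V0 cannot do this to any relevant extent.

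At stake is the precision of the trial's functional outcome with about 34 patients per arm, and whether the result can be read as more than an average number of steps.

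**Working it through.** **The plan's own figure.** The only sample-size figure is for the PHQ-9 primary outcome: f = 0.30, α = 0.05, r = 0.5, two groups, two measurements. For the between-group factor, λ = f²·N·m/(1+(m−1)r) = 0.09·68·2/1.5 = 8.16 with 1 and 66 df. This gives power 0.804, and N = 68 is the smallest even number reaching 80%. With 10% drop-out, 68/0.9 = 75.6, so 76. Both figures reproduce. Nothing comparable is given for mRS.

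**Efficiency of change against adjustment.** With a common SD σ and correlation r between V0 and follow-up:
- variance of change: 2σ²(1−r)
- residual variance after adjustment: σ²(1−r²)
- relative efficiency of change: RE = (1−r²)/(2(1−r)) = (1+r)/2

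If the adjusted analysis has 80% power at 34 per arm, the change score has power Φ(2.802·√RE − 1.96).

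| r | RE | power of change | total N to match 68 (68/RE) |
|---|---|---|---|
| 0.3 | 0.65 | 62% | 105 |
| 0.5 | 0.75 | 68% | 91 |
| 0.7 | 0.85 | 73% | 80 |
| 0.8 | 0.90 | 76% | 76 |

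Unequal SDs move this. If the V0 SD is 1.25 times the follow-up SD, the change score has 51% to 61% power over r of 0.3 to 0.8. If it is 0.8 times, 70% to 80%.

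**Does a mixed model avoid the loss?** The group-by-time pattern that the plan states for the primary endpoint does not avoid it by itself. With V0 as one of two outcome times, complete data and no constraint on the V0 means, the interaction is the change-score test. On one simulated trial the interaction z and the t statistic on change were both −2.032. Constraining the arms to a common V0 mean recovers nearly the efficiency of adjustment.

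**Simulation on the ordinal scale.** All inputs are assumed: V0 grades 0 to 5 with shares 4/14/20/22/30/10%; control day-84 grades 0 to 6 with shares 14/24/22/18/13/5/4%; common odds ratio 3.0; 34 per arm; 2,000 trials per setting. Here r is the latent correlation; the correlation between observed grades was 0.26, 0.42, 0.60 and 0.72.

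| Power | r = 0.3 | 0.5 | 0.7 | 0.85 |
|---|---|---|---|---|
| t-test on change | 54.7% | 69.3% | 84.4% | 94.8% |
| rank test on change | 53.1% | 67.3% | 82.5% | 94.3% |
| rank test on day-84 grade, V0 ignored | 68.2% | 72.0% | 68.7% | 70.5% |
| linear model adjusted for V0 | 69.1% | 78.3% | 86.9% | 95.5% |
| proportional odds adjusted for V0 | 74.1% | 82.7% | 90.4% | 98.3% |

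Loss of the t-test on change against the adjusted ordinal model: 19.4, 13.4, 6.0 and 3.5 points. It splits into two parts:
- subtracting instead of adjusting (linear adjusted minus change): 14.4, 9.0, 2.5 and 0.7 points
- treating the grade as linear (ordinal minus linear, both adjusted): 5.0, 4.4, 3.5 and 2.8 points

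At r of 0.3 and 0.5, ignoring V0 altogether beats subtracting it.

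**Type I error.** Simulated at odds ratio 1: the ordinal likelihood-ratio test 7.4%, 4.8%, 6.4%, 6.4%; linear adjusted 5.9%, 4.2%, 5.6%, 5.9%; t-test on change 5.8%, 4.3%, 5.1%, 5.2%. A rough correction replaces each power p, at observed size a, by Φ(Φ⁻¹(p) + z(1−a/2) − 1.96). At r = 0.3 the ordinal model falls from 74.1% to 68.2% and the change score from 54.7% to 52.1%, a loss of 16 points. At the other three correlations the loss becomes 12, 4 and 3 points. The ordinal model's edge over the linear adjusted model shrinks to about 2 to 3 points. The direction is unchanged and the sizes are slightly smaller.

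**The case against.** The strongest reply is that the article names an endpoint and not an analysis. A reader might infer that mRS is to be analysed as a difference of grades by an unadjusted rank test. The documents do not support that. The mixed-model route and its normality checks are stated for continuous secondary endpoints, mRS is not assigned to it, and the fallback is not described as unadjusted or as a test of change. The PHQ-9 outcome is also worded as a change, yet it goes to a mixed model. How V0 enters a model is commonly left to the analysis plan. This stands, so the point is conditional on the endpoint being analysed as worded.

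A reader might also infer that much of the power is lost because an ordinal scale is treated as continuous. That does not stand either. The linear part is small, and the total loss is small once r is 0.7 or more. The correlation, the distributions and the odds ratio are all assumptions. The simulation compares single-visit tests, not a mixed model over three follow-up visits.

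It is also fair to say that mRS is one of several secondary outcomes in a proof-of-concept trial sized on PHQ-9 only, and that the ordinal test runs somewhat above its nominal level at this sample size.

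What survives is that the endpoint text itself fixes V0 as something to be subtracted, and the stated routes offer nothing that corrects for this.

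**Conclusion.** The point holds in a limited form. The endpoint is defined as change from an acute-phase ordinal grade recorded about eight weeks before randomisation, with neither adjustment for V0 nor an ordinal method mentioned. Analysed as a difference from V0, or as a group-by-time contrast with V0 as an outcome and no common V0 mean, it is less precise than an analysis adjusted for V0. RE is (1+r)/2 with equal SDs. Under the assumed distributions and odds ratio of 3.0, the simulated loss against the adjusted ordinal model is about 13 to 19 points at r of 0.3 to 0.5 and 4 to 6 at r of 0.7 or more. Because the documents give no mRS correlation, where the trial lies in that range is unknown.

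There is no bias in the comparison of arms, and neither the sample size nor the primary conclusion is affected. The priority is modest, and the argument for acting is that the remedy is nearly free.

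**What to change.** - Define the endpoint as the mRS grade at each follow-up visit, with V4 as the main one. This agrees with Study description and study design, which places secondary outcomes at V4.
- State which recorded grade is the V0 value, and correct the V5 label.
- Analyse the grade with arm and V0 mRS as covariates, preferably in a proportional-odds model (a mixed version if all visits are used), and report a common odds ratio with confidence interval.
- Drop the normality gate and the transformation step for this outcome.
- Because the likelihood-ratio test can reach a type I error of about 7% at this size, take the p-value from a permutation test or support the result with a linear model adjusted for V0. The linear model alone would already remove most of the loss at r of 0.5 or less.

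The cost is a change of wording and a standard model, with no new data. The downside is the proportional-odds assumption, which should be examined and which the linear adjusted model does not need.

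### Five of the seven secondary outcomes start their clock before randomisation, which dilutes arm differences and costs precision; the PHQ-9 outcomes are not affected

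*Protocol article*

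**What the plan says.** All references are to the protocol article.

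- **Screening (V0).** Under Eligibility criteria, stroke patients "will be screened for depressive symptoms during the first days of their hospital stay".
- **Randomisation (V1).** Under Study description and study design, "patients with persisting depressive symptoms after eight weeks (56 days) at the baseline visit (V1) are randomized either to the intervention or the control condition".
- **Treatment.** Under Arms and interventions, both arms get "weekly phone calls over a period of 12 weeks, at the earliest time point of eight weeks after the acute stroke".
- **Event outcomes.** Under Secondary outcomes, major cardiovascular events are counted "within one year of the index event". Recurrent stroke or TIA has the same one-year window from the index event.
- **Change outcomes.** EQ-5D is defined as change in "score from Screening (V0) to days 84, 180 and 365 days (V2-V4"). The mRS entry reads "Change in modified Rankin Scale (mRS) from Screening (V0") and lists visits up to a V5, although V4 is the last visit. Return to work also runs from V0.
- **PHQ-9.** The primary outcome and the first secondary outcome both run from V1.
- **Mortality.** All-cause mortality is set at 14 months, with no origin given.
- **Visit days.** Under Arms and interventions, "At 84, 180 and 365 days after inclusion standardized postal questionnaires are sent to the patients". Study description and study design speaks of follow-up to one year after enrolment, and of day 84 and day 365 without naming day 0. The abstract lists V1 first and then 84, 180 and 365 days.

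**The concern.** A randomised comparison is informative about what happens after allocation. Two event outcomes start at the stroke and three further outcomes start at V0, so all five take in about eight weeks before V1. A stroke or myocardial infarction in that interval counts as an outcome event although no arm had been assigned. Death cannot occur in it, because only survivors are randomised. For EQ-5D, mRS and return to work, the early recovery between V0 and V1 is added to whatever happens under treatment.

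At stake is the sensitivity of these five secondary outcomes: any arm difference is pulled towards none, or measured with more noise. There is also an internal mismatch. The PHQ-9 outcomes use the randomisation visit as origin and the other outcomes do not, and no single day 0 fits every stated time point.

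**Working it through.** **1. The plan's own figure.** Inputs from Study description and study design: f = 0.30, r = 0.5, two groups, α = 0.05, power 0.80. With m = 2 measurements, the between-group test has λ = N·f²·m/(1 + (m−1)r) = 68 × 0.09 × 2/1.5 = 8.16 on 1 and 66 degrees of freedom, which gives power 0.804. So 68 reproduces. The time and interaction tests need only 24. With 10% drop-out, 68/0.9 = 75.6, hence 76. None of this depends on the outcome clocks.

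**2. Count of outcomes by origin.**

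| Secondary outcome | Origin | Before V1? |
|---|---|---|
| PHQ-9 change | V1 | no |
| EQ-5D change | V0 | yes |
| mRS change | V0 | yes |
| Return to work | V0 | yes |
| Major cardiovascular events | index event | yes |
| Recurrent stroke/TIA | index event | yes |
| All-cause mortality, 14 months | not stated | unclear |

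Five of seven start before randomisation.

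**3. Event window.** Share before allocation: 56/365 = 15.3%. Days left after it: 365 − 56 = 309. The share is larger if V1 falls later.

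**4. Which clock the visit days use.**
- *Counted from V1:* V2 falls 84 = 12 × 7 days after V1, at the end of the calls. V4 falls 56 + 365 = 421 days after screening, or 421/30.44 = 13.8 months. That agrees with the 14-month mortality point if mortality is counted from the stroke. The one-year event window then closes 421 − 365 = 56 days before V4, so a vascular death in that gap counts towards mortality but not towards major cardiovascular events.
- *Counted from the stroke or screening:* the event window ends at V4. But V2 falls 84 − 56 = 28 days after V1, at week 4 of 12, and the 14-month point lies beyond the last visit.

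The first reading fits more of the text, but it leaves the event window out of step with V4.

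**5. Dilution of a risk ratio.** Let s be the share of control-arm events that fall before V1. These events are equal between arms in expectation, so RR(observed) = s + (1 − s)·RR(true). The article gives no event rates; s and a true RR of 0.70 are assumptions.

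| s | Observed RR |
|---|---|
| 10% | 0.10 + 0.90 × 0.70 = 0.730 |
| 15.3% | 0.153 + 0.847 × 0.70 = 0.746 |
| 25% | 0.25 + 0.75 × 0.70 = 0.775 |
| 35% | 0.35 + 0.65 × 0.70 = 0.805 |

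The 15.3% row corresponds to a constant event rate.

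**6. Precision of change scores.** With equal SDs, the variance of a change score is 2σ²(1 − r), so the ratio of change from V0 to change from V1 is (1 − r(V0,V2))/(1 − r(V1,V2)). Take r(V1,V2) = 0.5, borrowed from the PHQ-9 calculation, and let r(V0,V2) vary as an assumption. For comparison, the last column gives the variance when V0 is a covariate, σ²(1 − r²).

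| r(V0,V2) | Change from V0 (σ²) | Ratio to change from V1 | V0 as covariate (σ²) |
|---|---|---|---|
| 0.2 | 1.6 | 1.6 | 0.96 |
| 0.3 | 1.4 | 1.4 | 0.91 |
| 0.4 | 1.2 | 1.2 | 0.84 |
| 0.5 | 1.0 | 1.0 | 0.75 |

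The V1 value as covariate gives 1 − 0.5² = 0.75. mRS is ordinal and return to work is binary, so for these two the table shows direction only.

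**The case against.** The other side has a good deal on its side.

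- **The main outcome is sound.** A reader might infer that all outcomes, including the primary, absorb pre-randomisation time. They do not: both PHQ-9 outcomes run from V1, and only PHQ-9 underlies the sample size. This stands in full.
- **Day 84.** A reader might infer that the primary measurement falls 28 days after V1, with most calls still to come. The abstract's order of visits, the 84-day length of the call period and the 14-month figure all point to counting from V1, and the 56 days can be read simply as the V0–V1 interval. The 28-day reading is possible only because day 0 is not named. What remains is a wording clarification.
- **No bias.** Pre-allocation events and recovery are balanced in expectation, and survival to V1 is required in both arms. This stands.
- **Size.** Much larger losses could be produced by choosing a higher r(V1,V2) or by assuming that a third or more of events come early. The article supports neither choice, and with r = 0.5 for both pairs the change-score loss is nil. This is why ranges are given above.
- **Missing schedule.** Table 1 is not legible in the available text and may name day 0, or show EQ-5D and mRS at V1. Mixed models are planned, and their baseline handling may properly sit in the analysis plan. This limits what can be said about V1 data. It does not alter the origins written under Secondary outcomes.
- **Purpose.** A one-year rate from the stroke is a natural descriptive figure, and a proof-of-concept trial of 76 claims no power for vascular events. That lowers the priority but does not justify using that window to compare arms.

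**Conclusion.** The point holds for five secondary outcomes. At least 15% of the window for major cardiovascular events and recurrent stroke/TIA precedes allocation. If visit days count from V1, about 56 days of randomised follow-up before V4 are also dropped. EQ-5D, mRS and return to work carry about eight weeks of pre-allocation recovery.

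The cost is dilution and lost precision, not bias. A true risk ratio of 0.70 would appear as about 0.75 if 15% of control-arm events fell before V1. Raw change from V0 would have 1.0 to 1.6 times the variance of change from V1, for r(V1,V2) = 0.5, equal SDs and r(V0,V2) between 0.5 and 0.2. These sizes are illustrations, because the article states neither event rates nor correlations for these outcomes.

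The primary outcome, the secondary PHQ-9 outcome and the sample sizes are untouched. The definitions are worth correcting because the change is cheap and the stated origins disagree with the trial's own randomisation visit.

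**What to change.** 1. Count major cardiovascular events, recurrent stroke/TIA and deaths from randomisation (V1) to V4. Report events between V0 and V1 as baseline history. A one-year rate from the stroke can still be given as a description.
2. Analyse EQ-5D and mRS at V2 to V4 adjusted for the V1 value if it is recorded. If it is not, use V0 as a covariate instead of taking change from V0. Treat work resumed before V1 as baseline status in the same way.
3. As a clarification, state that days 84, 180 and 365 count from V1, and reconcile with this the terms *inclusion* and *enrolment*, the 14-month mortality point and the V5 in the mRS entry.

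**Cost.** Outcome wording changes in the protocol and registry entry, dated before any analysis by arm. The V1-to-V4 window is again 365 days, so the number of counted events falls only if events cluster early, and the events removed carry no information on treatment. If EQ-5D and mRS are not already taken at V1, recording them adds a short assessment at an existing visit; the V0 covariate avoids even that. Numbers to recruit do not change.
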